## Abstract

**Background:**

Cognitive behaviour therapy (CBT) is an effective treatment for depression. However, CBT is a complex therapy that requires highly trained and qualified practitioners, and its scalability is therefore limited by the costs of training and employing sufficient therapists to meet demand. Behavioural activation (BA) is a psychological treatment for depression that may be an effective alternative to CBT and, because it is simpler, might also be delivered by less highly trained and specialised mental health workers.

**Methods/Design:**

COBRA is a two-arm, non-inferiority, patient-level randomised controlled trial, including clinical, economic, and process evaluations comparing CBT delivered by highly trained professional therapists to BA delivered by junior professional or para-professional mental health workers to establish whether the clinical effectiveness of BA is non-inferior to CBT and if BA is cost effective compared to CBT. Four hundred and forty patients with major depressive disorder will be recruited through screening in primary care. We will analyse for non-inferiority in per-protocol and intention-to-treat populations. Our primary outcome will be severity of depression symptoms (Patient Health Questionnaire-9) at 12 months follow-up. Secondary outcomes will be clinically significant change and severity of depression at 18 months, and anxiety (General Anxiety Disorder-7 questionnaire) and health-related quality of life (Short-Form Health Survey-36) at 12 and 18 months. Our economic evaluation will take the United Kingdom National Health Service/Personal Social Services perspective to include costs of the interventions, health and social care services used, plus productivity losses. Cost-effectiveness will explored in terms of quality-adjusted life years using the EuroQol-5D measure of health-related quality of life.

**Discussion:**

The clinical and economic outcomes of this trial will provide the evidence to help policy makers, clinicians and guideline developers decide on the merits of including BA as a first-line treatment of depression.

**Trial registration:**

Current Controlled Trials ISRCTN27473954

## Background

Clinical depression is one of the most common and debilitating of the psychiatric disorders. It accounts for the greatest burden of disease among all mental health problems, and is expected to become the second largest amongst all general health problems by 2020 [1]. Lifetime prevalence has been estimated at 16.2% and rates of co-morbidity and risk for suicide are high [2-4]. Depression is recurrent, with over three-quarters of all people who recover from one episode going on to have at least one more [5]. Without treatment many cases become chronic, lasting over 2 years in one-third of individuals. In the UK, the annual costs of depression and anxiety to the economy are estimated at £17bn in lost output and direct health care costs, with a £9bn impact on the Exchequer through benefit payments and lost tax receipts [6].

Antidepressant medication (ADM) and cognitive behaviour therapy (CBT) are the two treatments with most evidence of effectiveness; both are recommended by the National Institute for Health and Care Excellence (NICE) [7]. Problems with ADM include side effects, poor patient adherence and relapse risk on ADM discontinuation. Service-user organisations and policy think tanks advocate greater availability of psychological therapies, which many people prefer [8]. CBT, which is of similar efficacy to ADM [9], has several advantages: 1) it reflects the desire of many service users for non-pharmacological treatment; 2) it has no physical side-effects; and 3) it modifies the illness trajectory in that benefits continue after the end of treatment thereby reducing rates of recurrence [10]. However, CBT has several limitations: 1) its complexity may make it difficult to learn to implement in a competent fashion; 2) there is some evidence that its efficacy is dependent upon the skill of the individual practitioner; 3) patients are required to learn high-level skills; and 4) the high costs of training and employing sufficient therapists limits access to CBT.

As a consequence of the problems above, many people do not receive adequate treatment and even, when treatment is given, many respond only partially or not at all [11]. For example, despite the recent UK government initiative in England - ‘Improving Access to Psychological Therapies’ (IAPT: http://www.iapt.nhs.uk/) - no more than 15% of people with depression will receive National Health Service (NHS)-delivered CBT and only 50% will recover [12]. It is therefore important to continue to test promising new treatments, especially if: there are indications that such treatments reduce the risk of symptom return; are applicable to a wide range of depressed people including those with high severity; are easy to implement in clinical practice and are therefore potentially more accessible [13]; and are a cost-effective use of resources. Indeed, in order to meet public and professional expectations, health services require simple, equivalently effective, easily implemented psychological treatments for depression that can be delivered by less specialist (albeit appropriately competent) junior or para-professional health workers to treat many more people with depression in a more cost-effective manner.

Behavioural activation (BA) is a psychological treatment based on behavioural theory that alleviates depression by focusing directly on changing behaviour [14-16]. This theory states that depression is maintained in part by avoidance of normal activities. As people withdraw and disrupt their basic routines, they become isolated from positive reinforcement opportunities in their environment. The combination of increased negative reinforcement with reduced positive reinforcement results in a cycle of depressed mood, decreased activity and avoidance which maintains depression [15]. BA systematically disrupts this cycle, initiating approach-oriented behaviours in the presence of negative mood, when people’s natural tendency is to withdraw or avoid [17,18]. Although CBT incorporates some behavioural elements, these commonly focus on increasing rewarding activity and initiating behavioural experiments to test specific beliefs. In contrast, BA targets avoidance from a contextual, functional approach not found in CBT - that is, BA focuses on understanding the function of behaviour and replacing it accordingly. BA also explicitly prioritises the treatment of negatively reinforced avoidance and rumination. Furthermore, because the BA rationale is simpler, it should be easier to understand and operationalise for both patients and mental health workers than CBT, where activity is also increased but the primary techniques focus on changing maladaptive beliefs [19]. Moreover, there is some evidence that CBT is less effective when delivered by less competent therapists [9,20].

In the UK, CBT is delivered by professionally qualified senior mental health workers (mainly clinical psychology, nursing, occupational therapy, social work or counselling), who have obtained a further 1 year full time post-graduate qualification in CBT. Their training is long and expensive and their employment grade is costly compared to junior professionals or para-professional mental health workers who deliver much of the routine mental health care in the UK. The relative simplicity of BA treatment may make it easier and cheaper to train para-professional mental health workers in its application than CBT, the argument of ‘parsimony’ first advanced by one of the early proponents of this approach, Neil Jacobson, more than 10 years ago [15].

### Limitations of previous trials

We conducted a meta-analysis of randomised controlled trials of BA [21] where we first found a clinical effect size in terms of a reduced depression score of −0.70 SD units from twelve studies (n = 459; 95% CI −1.00 to −0.39; *P* < 0.001) comparing behavioural treatments to controls using experienced therapists. We then found twelve studies comparing behavioural treatments with CBT (n = 476) and showed that behavioural treatments had equivalent outcomes to CBT (pooled SMD 0.08; 95% CI −0.14 to 0.30, *P* = 0.46). Meta regression of results exploring association between baseline severity and effect size identified a statistically significant result in favour of BA (meta-regression b-coefficient −0.05; 95% CI −0.10 to −0.01; *P* = 0.04).

However, many of the trials were of limited methodological quality, all were under-powered for comparing treatments, and most did not utilise diagnostic interviews for trial inclusion. Treatments in many cases did not conform to modern clinical protocols for BA. Long-term outcomes were rarely reported, with average follow-up only to 4 months. These results have been replicated in two recent Cochrane reviews of behavioural therapies [22,23] which concluded that there was only low- to moderate-quality evidence that behavioural therapies and other psychological therapies were equally effective and called for ‘Studies recruiting larger samples with improved reporting of design and fidelity to treatment’ to ‘improve the quality of the evidence’ [22] (page 2).

Therefore, the existing trial data are insufficient to provide certainty that BA should be a first-line treatment for depression and these limitations led to NICE in the UK regarding the evidence for BA as equivocal and of insufficient strength to recommend BA for first-line routine NHS depression treatment [7]. Consequently, NICE made a clear research recommendation “to establish whether behavioural activation is an effective alternative to CBT” using a study “large enough to determine the presence or absence of clinically important effects using a non-inferiority design” [7] (page 256).

### Pilot work preceding this trial

In order to test uncertainties around our main objectives, we piloted BA in a phase II randomised controlled trial to examine whether mental health workers without previous specialist training in psychological therapy can effectively treat depressed people using BA [24]. We compared BA against usual care. Relatively junior NHS mental health workers ('band 5' - equivalent to a basic grade qualified mental health nurse) with no previous formal training or experience in psychotherapy delivered BA. These workers received 5 days training in BA and subsequent 1-hour clinical supervision fortnightly from a clinical nurse consultant or trained psychotherapist. Intention-to-treat (ITT) analyses indicated a difference in favour of BA of −15.79 (n = 47; 95% CI −24.55 to −7.02) on depression (Beck Depression Inventory-II), an effect size of −1.15 SD units (95% CI −0.45 to −1.85). We also found a quality-adjusted life year (QALY) difference in favour of behavioural activation of 0.20 (95% CI 0.01 to 0.39, *P* = 0.042), incremental cost-effectiveness ratio of £5,756 per QALY and a 97% probability that behavioural activation is more cost-effective at a threshold value of £20,000 [25].

### Objectives

1 What is the clinical effectiveness of BA compared to CBT for depressed adults in terms of depression treatment response at 12 and 18 months?

2 What is the cost-effectiveness of BA compared to CBT at 18 months?

It is hypothesised that BA is non-inferior compared to CBT in reducing depression severity but that BA will be less costly and thus more cost-effective than CBT.

In addition, we will undertake a secondary process evaluation to investigate the moderating, mediating and procedural factors in BA and CBT that influence outcome.

### Methods/Design

COBRA is a two-arm, non-inferiority, patient-level randomised controlled trial, including clinical, economic and process evaluation for people with depression. We will test the effectiveness of a psychological intervention for depression - BA - against CBT, the current gold standard evidence-based psychological treatment for depression. The rationale for a non-inferiority trial is that we wish to establish whether the clinical effectiveness of BA is not substantially inferior to CBT and to determine if BA represents a viable first choice of treatment in the management of depression. Accordingly, we have powered our trial on the basis of clinical non-inferiority, and will analyse our data accordingly [26,27].

### Setting and participants

We will recruit participants from the electronic case records of primary care general practices in three UK sites: Devon, Durham and Leeds. Eligible participants will be aged 18 and older with DSM Major Depressive Disorder assessed by standard clinical interview (Structured Clinical Interview for Depression; SCID) [28]. People will be excluded if they are alcohol or drug dependent, are currently acutely suicidal or have made a suicide attempt in the previous 2 months, are cognitively impaired, or have a bipolar disorder or psychosis/psychotic symptoms. We will also exclude people currently in receipt of psychological therapy.

### Randomisation, concealment of allocation, and blinding

Participants will be allocated in a 1:1 ratio to either the BA or CBT arms stratified according to their symptom severity on the Patient Health Questionnaire 9 (PHQ-9) [29] (PHQ-9 <19 versus ≥19), antidepressant use (currently using anti-depressants or not) and recruitment site. A computer-based system will allocate the first 20 participants to each arm on a truly random basis. For subsequent participants, allocation will be minimised to maximise the likelihood of balance in stratification variables across the two study arms. Concealment will be ensured by use of an externally administered password-protected trial website and retaining a stochastic element to the minimisation algorithm. The computer-based allocation and website will be setup and maintained by the accredited Peninsula Clinical Trials Unit, independent of the trial. The participant’s details will be sent to the relevant mental health worker to alert them to contact this person and begin treatment.

All research measures will be applied to both groups of participants equally. Researchers will be blind to group allocation, which will occur after baseline assessments. At follow-up, researchers will be instructed to maintain blindness by reminding participants of the confidential nature of their treatment and the need not to discuss this with researchers. We will test blindness by asking researchers to indicate at follow-up which treatment they believe the participants received and analyse any correlation with outcome.

### Recruitment

Randomised controlled trials are vulnerable to selection bias and threats to external validity if there are systematic differences in behaviour between referring clinicians. We will minimise this potential bias by recruiting participants through searching general practice records and referral logs from primary care to local depression and anxiety treatment services, rather than by direct referral from general practitioners (GPs). We will identify suitable participants by examining electronic case records for all patients in each general practice or treatment service. The GP search will be limited to people seen by their GPs in the previous 2 months who have been allocated at least one identification code in their electronic records. Several such codes are widely used by general practitioners to classify patients. Practice staff or Research Network Clinical Studies Officers will conduct searches. The list of potentially suitable participants will be reviewed by GPs to identify any patients whom have known exclusion criteria. The remaining patients will be written to by their GP practice, inviting them to take part in the study. For patients already referred to local psychological therapies services, we will contact those on the waiting list. A short participant information sheet, stamped addressed envelope and a ‘Permission for Researcher to Contact’ form to allow a researcher to contact them, will accompany letters. If potential participants do not return the form, they will be contacted by telephone by practice staff, practice based Research Network Clinical Studies Officers or service administrators to check they have received the letter and asking them if they wish to participate in the COBRA trial. Potential participants identified by either written or telephone routes will be initially telephone screened by researchers to confirm the presence of depressive symptoms, and to explain the trial fully. If positive on the screen, potentially eligible participants will be interviewed face-to-face by researchers to confirm eligibility, take consent, conduct a diagnostic interview and collect baseline measures. Eligible, fully informed and consenting participants will then be entered into the study and randomisation (See Figure 1).

**Figure 1 F1:**
[figure not shown]
**Consort diagram describing flow of patients through study.** GP, general practitioner.

### Trial interventions

We have specified our BA and CBT for depression intervention protocols in line with (a) the original treatment protocols [9,15,17-19,30,31] and (b) NICE recommendations [7] for duration and frequency of BA and CBT. To recognise realities of real world clinical presentations, our protocols will include behavioural and cognitive strategies for managing comorbidity, particularly anxiety, where this is present in addition to depression. Participants will receive a maximum of 20 sessions over 16 weeks with the option of four additional booster sessions [7].

### Behavioural activation

The overall goal of BA is to re-engage participants with stable and diverse sources of positive reinforcement from their environment and to develop depression management strategies for future use. Mental health workers delivering BA will follow a revised treatment manual based on that used in our Phase II trial [24] and previous international studies [30], incorporating recommendations from NICE Guidelines [7] and advice from our international collaborators, [name] and [name]. Sessions will be face-to-face, of 1-hour duration, with the option of being conducted up to twice weekly over the first 2 months and weekly thereafter. They will consist of a structured programme increasing contact with potentially antidepressant environmental reinforcers through scheduling and reducing the frequency of negatively reinforced avoidant behaviours. The central behavioural technique will be functional analysis of the participant’s problems, based on a shared formulation drawn from the behavioural model in the early stages of treatment, thereafter developed with the patient throughout their sessions. Specific BA techniques include the use of a functional analytical approach to develop a shared understanding with patients of behaviours that interfere with meaningful, goal-oriented behaviours and include self-monitoring, identifying ‘depressed behaviours’, developing alternative goal-orientated behaviours and scheduling. In addition, the role of avoidance and rumination will be addressed through functional analysis and alternative response development incorporating recent trial evidence [32].

Workers will be selected from NHS band 5 mental health workers such as mental health nurses and para-professional Psychological Wellbeing Practitioners [33], and will receive 5 days training in BA. In line with the programme developed and tested in our Phase II trial [24], training will focus upon the rationale and skills required to deliver the BA protocol for depression and include sections on behavioural learning theory and its application to depression, developing individualised BA formulations and specific techniques used in sessions. Training will be a mix of presentation and role-play with repeated practise and feedback. Workers will be competency-assessed at the end of training using standardised marking criteria consistent with the BA protocol and further training given if competency is not demonstrated in practical clinical exercises. BA workers will receive subsequent 1-hour clinical supervision fortnightly from the three site leads or other members of the trial team, clinically qualified in BA.

### Cognitive behaviour therapy

The overall goal of CBT is to alter the symptomatic expression of depression and reduce risk for subsequent episodes by correcting the negative beliefs, maladaptive information processing and behavioural patterns presumed to underlie the depression. Therapists delivering CBT will follow a treatment protocol based on the standard manuals published by Beck and colleagues [19,31], the manual used in our recent trial [34] and additional advice and training resources from our US collaborator, [name]. Sessions will be face-to-face, of 1-hour duration, with the option of being conducted up to twice weekly over the first 2 months and weekly thereafter. They will consist of a structured, collaborative programme. Treatment begins with agreeing a problem list and goals for therapy, patients learning the CBT model, behavioural change techniques, and moves on to identifying and modifying negative automatic thoughts, maladaptive beliefs and, if indicated, underlying core beliefs. In later sessions, learning is translated to anticipating and practicing the management of stressors that could provoke relapse in the future. Specific CBT techniques include scheduling activity and mastery behaviours, the use of thought records and modifying maladaptive beliefs and rumination content. The behavioural elements in CBT focus on increasing activity with practical behavioural experiments to test specific cognitive beliefs. CBT will not take the contextual, functional analytical approach of the BA trial arm.

CBT will be delivered by senior mental health workers with a specialist postgraduate diploma in ‘high-intensity’ CBT from an accredited University course. These workers are employed at NHS band 7. They will also receive a 5-day orientation training to the specific CBT protocol [19,31], including its adaptation for co-morbidities, cognitive theory of depression, developing individualised cognitive formulations and specific techniques used in sessions. Therapists will be competency assessed at the end of training using standardised marking criteria consistent with the CBT protocol and further training given if competency is not demonstrated. CBT therapists will receive subsequent 1-hour clinical supervision fortnightly from established supervisors in the three sites with advice from other members of the trial team, clinically qualified in CBT.

### Intervention fidelity

We will assess the quality of and adherence to BA and CBT clinical protocols using audiotapes of therapy sessions. A random sample of tapes, stratified by therapist, therapy session and intervention will be sent to independent experts in both treatments for competence rating using the Cognitive Therapy Scale - Revised [35] for CBT and the Quality of Behavioral Activation Scale [36] for BA.

### Outcomes

We will conduct follow-up assessments at 6, 12, and 18 months post-baseline assessment. Our primary outcome will be self-reported depression severity and symptomatology as measured by the PHQ-9 [29] at 12 months. The PHQ-9 is a nine-item questionnaire that records the core symptoms of depression with established excellent specificity and sensitivity characteristics in a UK population [37]. Our secondary outcomes will be DSM Major Depressive Disorder status and number of depression free days between follow-ups, assessed by standard clinical interview (SCID) [28], anxiety assessed by the Generalised Anxiety Disorder-7 [38], and health-related quality of life (Short-Form Health Survey-36) [39].

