
The primary analysis will compare primary and secondary outcomes between BA and CBT groups at 12 months after randomisation adjusting for baseline outcome values and stratification variables (symptom severity, site, antidepressant use) and fitting therapist as a random effects variable. The one-sided 97.5% CI for the between-group difference will be estimated and non-inferiority of BA compared to CBT will be accepted (in a 0.025 level test) if the lower bound of the 97.5% CI lies within the non-inferiority margin of −1.90 in PHQ-9 score. If non-inferiority is shown, we will then test for superiority of CBT over BA (that is, lower bound of the 97.5% CI lies above 0). We will check for non-equivalence at all follow-up points using the same approach. Secondary analyses will be undertaken to compare groups at follow-up across 6, 12, and 18 months using a repeated-measures approach. The analysis will be extended to fit interaction terms to explore possible differences in treatment effect in baseline symptom severity and antidepressant usage. Sensitivity analysis, making different assumptions about the imputation model used, will be conducted for both primary and secondary analyses to assess the likely impact of missing data. Models will be fitted using generalized linear mixed models and undertaken in STATA v.11, STATA, StataCorp LP, [name]. We will also analyse the relative proportions of participants meeting criteria for “recovery” (proportions of participants with PHQ-9 scores ≤9) and “response” (50% reduction in scores from baseline) on the PHQ-9.

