### Forecast execution dates

The preparatory period started in March 2012. Recruitment is running from September 2012 to June 2014. Follow up will last 18 months, at 6 (T1), 12 months (T2) and 18 (T3) months after randomisation. Data analysis and reporting will take another 6 months. The entire study period will last for 48 months.

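### For the two SCID secondary outcomes the baseline-value covariate is constant or absent, so baseline severity enters only as a PHQ-9 split; minor, with one wording clarification

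*Protocol article*

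**What the plan says.** In the protocol article, Outcomes lists among the secondary outcomes DSM MDD status and "number of depression free days between follow-ups, assessed by standard clinical interview (SCID"). The same paragraph fixes the visits: "We will conduct follow-up assessments at 6, 12, and 18 months post-baseline assessment". Forecast execution dates repeats them: "Follow up will last 18 months, at 6 (T1), 12 months (T2) and 18 (T3) months after randomisation".

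Data analysis gives a single covariate rule. The analysis will "compare primary and secondary outcomes between BA and CBT groups at 12 months after randomisation adjusting for baseline outcome values and stratification variables", with therapist as a random effect. It makes no exception for any secondary outcome. The section adds that the check is repeated at all follow-up points and that groups are compared across 6, 12 and 18 months by repeated measures.

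Two other places matter. Setting and participants makes the diagnosis an entry condition: "Eligible participants will be aged 18 and older with DSM Major Depressive Disorder assessed by standard clinical interview". The section on randomisation defines the symptom-severity stratum as PHQ-9 below 19 versus 19 or above.

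**The concern.** A rule to adjust for the baseline value of the outcome works for PHQ-9, GAD-7 and SF-36, which vary between patients at entry. It has nothing to act on for the two SCID outcomes. Everyone eligible has MDD at entry, so baseline MDD status is the same for all. Depression-free days count time after entry, and the article describes no pre-entry counterpart.

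What remains in these two models is the list "adjusting for baseline outcome values and stratification variables (symptom severity, site, antidepressant use"). Severity then enters as a two-level split, although the full baseline PHQ-9 score is needed to form that split and to adjust the primary outcome. At stake is precision on two secondary outcomes.

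A smaller point concerns the counting window. Visits called follow-ups occur at 6, 12 and 18 months. Read strictly, the time between them is months 6 to 12 and 12 to 18. Baseline to month 6 contains the whole treatment course ("Participants will receive a maximum of 20 sessions over 16 weeks").

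**Working it through.** **1. What the covariate rule does for MDD status.** A column that is constant across patients is a multiple of the intercept. Check on simulated data (n = 352, logistic model):

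- The design matrix with intercept, arm and one stratifier has rank 3.
- Adding a constant baseline-MDD column gives 4 columns, still rank 3.
- The arm coefficient is −0.0613 in both fits.

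The term drops out, and the treatment estimate is neither changed nor biased.

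**2. What it does for depression-free days.** No baseline value is described, so there is no column to enter. The stratification variables and the therapist effect remain.

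**3. How much severity information the split keeps.** From the article: the cut at 19. Assumed: baseline PHQ-9 normal with mean 18 and SD 4.5, rounded and limited to 5–27. The squared correlation between the score and the indicator for 19 or above is then 0.65, so the split keeps about 65% of the linear information.

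**4. Precision lost.** Let r be the correlation of baseline PHQ-9 with a continuous outcome (assumed 0.3 to 0.5). The residual variance is proportional to 1 − 0.65r² with the split and to 1 − r² with the continuous score. Other covariates and the therapist effect are ignored.

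| r | split | continuous | variance ratio | variance saved |
|---|---|---|---|---|
| 0.3 | 0.942 | 0.910 | 1.035 | about 3% |
| 0.4 | 0.896 | 0.840 | 1.067 | about 6% |
| 0.5 | 0.838 | 0.750 | 1.117 | about 10% |

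The ratios equal about 3.5% to 12% more patients for that outcome. Baseline means of 17 to 19 give similar ratios, the largest being 1.12 to 1.13 at r = 0.5 and mean 17. No gain was computed for the binary outcome.

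**5. The counting window.** The strict reading covers 12 of 18 months. The omitted third contains the 16 weeks of treatment: 16 × 7 / 30.44 = 3.7 months.

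To see what this could do, take a two-state model with everyone in episode at entry. Assume median recovery of 3 versus 5 months and median time to relapse of 24 months. The simulated arm difference is 24.8, 28.9 and 20.6 days in the three intervals.

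- To month 18: 24.8 + 28.9 + 20.6 = 74.3 days in full, and 28.9 + 20.6 = 49.5 days on the strict reading. That is 33% fewer days.
- To month 12: 53.7 days in full and 28.9 on the strict reading. That is 46% fewer.
- Per month counted: 74.3/18 = 4.13 and 49.5/12 = 4.13 to month 18; 53.7/12 = 4.48 and 28.9/6 = 4.82 to month 12.
- Difference divided by SD: 0.494 in full and 0.442 on the strict reading to month 18; 0.464 and 0.422 to month 12.

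With two other assumed input sets (recovery 4 versus 6 months, relapse 24; recovery 3 versus 4 months, relapse 18), the standardised difference falls from 0.370 to 0.348 and from 0.282 to 0.247 at month 18. At month 12 it falls from 0.342 to 0.330 and from 0.265 to 0.235. Over all three sets the fall is about 3% to 12%.

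**6. Consistency of the sections.** Data analysis examines outcomes at every follow-up point, month 6 included. On the strict reading, depression-free days have no month-6 value. On the reading that each count runs from the previous assessment, they do.

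**The case against.** The strongest reply is that this is a condensed article that defers to an a priori statistical analysis plan, not shown here. Covariates for a particular secondary outcome and the exact counting window are normally settled there. That carries weight and keeps the point minor. It does not remove it, because the article states a blanket rule that two of the outcomes it names cannot use.

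A reader might infer that the rules break down for these outcomes. The article does not support that: a constant covariate disappears without effect, an absent one is skipped, and both outcomes can be analysed with the remaining terms.

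A reader might also infer that the first six months are excluded, that a third to nearly half of any arm difference is thereby lost, and that this favours non-inferiority. None of this holds:

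- The article never says that the first interval is excluded. Its phrase can equally mean since the previous assessment, and Forecast execution dates describes follow-up as lasting 18 months.
- The 33% and 46% mostly reflect counting fewer months. The spread shrinks too, so the ability to tell the arms apart falls far less.
- The only margin is 1.90 points on PHQ-9. Depression-free days have no margin and play no part in declaring non-inferiority.

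Finally, if symptom severity in the Data analysis list were meant as the continuous score, the precision loss would vanish. The randomisation section defines that stratification variable as a split, so the text would need to say so.

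**Conclusion.** The point holds as a minor one on two secondary outcomes. For MDD status and depression-free days, adjusting for the baseline outcome value adds nothing, and baseline severity enters only through the <19/≥19 stratum. Nothing is biased. For a continuous outcome such as depression-free days, about 3% to 10% of the variance of the treatment effect could be saved. That figure rests on an assumed correlation of 0.3 to 0.5 and an assumed baseline PHQ-9 distribution; the gain for MDD status is not quantified.

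The counting window is a wording ambiguity, not a demonstrated omission. It deserves a clear statement because Outcomes and Data analysis agree only on one of the two readings. The primary PHQ-9 analysis, the margin and the sample size are unaffected.

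**What to change.** In Data analysis, add a sentence such as: for DSM MDD status and depression-free days, which have no usable baseline value, the models adjust for continuous baseline PHQ-9 in addition to the stratification variables.

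In Outcomes, as a clarification, state that depression-free days are counted from baseline to 6 months, 6 to 12 months and 12 to 18 months. The month-6 interview must then ask about the time since baseline. Since recruitment is under way, it is worth confirming that it does.

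The cost is two sentences, with no extra patients or visits and no new baseline measure. The one statistical downside is that the added covariate slightly changes the conditional odds ratio for MDD status, so its report should name the covariates.
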